### Interventionists

#### Intervention 1

Interventionists are care counsellors of the two participating LTC insurances. According to the training manual, the care counsellors are trained in a two-day workshop (e.g. short presentations, role-plays, group work) with additional telephone-based training and supervision by the study team during a training period of 2 to 3 months before delivering intervention 1 in the study. After the initial training period the care counsellors are supervised by registered psychotherapists (no members of the study team) in monthly telephone contacts during their active participation in the study. Major components of these telephone calls are the delivery of the problem-solving intervention, coping with difficult interactions during counselling sessions, and mental hygiene. The last two optional aspects are included as a form of reward for participating and investing hours of work in the study. The manual for supervisors has been developed together with experts in workplace health promotion for caring professions. Supervisors of the care counsellors have received a one-day on-site training (TH from the ReDiCare study group, KP) and optional additional phone calls with the principal investigator (KP) to discuss open questions. For the intervention, 14 counsellors (home visit plus telephone / AOK Bavaria: 10 counsellors; telephone based only / AOK Baden-Württemberg: 4 counsellors) and 3 supervisors are trained. Care counsellors do not receive any extra money for participating in the study. Supervision for care counsellors is provided on a per hour fee basis for psychotherapists.

#### Intervention 2

Interventionists are CBT therapists. Based on the Tele.TAnDem.Plus^+^ manual, the CBT therapists are trained in a 1 day workshop. One part of the training focuses on the original Tele.TAnDem CBT intervention strategies [23, 26]. The other part of the training focuses on specific demands of various diseases in old age (e.g. stroke, cancer, Parkinson’s disease, and incontinence) as well as typical therapeutic problems and appropriate therapeutic strategies for these diseases and typical caregiver demands and problems. After the initial training, CBT therapists are supervised by GW in regularly group or telephone contacts (4 to 6 times per year and on demand) during the intervention period to ensure treatment integrity. Telephone therapy sessions in intervention 2 are paid on a per hour fee basis for psychotherapists. All therapy sessions are audiotaped to analyse treatment integrity.

### Control group

Participants allocated to the control group are informed about the regular care counselling offered by the insurance of the care recipient after randomisation. Each caregiver of the control group receives an allowance of 50 € for participation in the study.

### Information provision and routine care in all study groups

If a care recipient receives home care solely from informal caregivers, the federal law states that caregivers have to be visited (depending on the care level) two to four times a year by professional caregivers for information and training to ensure a sufficient quality of care. Caregivers in both conditions of this study receive this form of consultation as well as all other benefits of their health and long-term insurance. To increase the likelihood that participants of the control group remain in the study and to provide comparable general information on caregiver topics across the two states and participating LTC insurances, all participants receive nine printed information letters on caregiving (e.g. benefits of the long-term care insurance, relaxation, depression) by the study team.

### Measures

Table 3 provides an overview of the primary and secondary outcomes

**Table 3 Tab3:**
[figure not shown]
Assessments

### Primary outcome measure

#### Depressiveness

Depressive symptoms of informal caregivers are assessed by the 20-item Centre for Epidemiological Studies Depression scale (CES-D) [46, 47]. Total scores range from 0 to 60 with a score of ≥16 as an indicator of caregivers at risk for clinical depression.

### Secondary outcome measure

#### Physical complaints

Subjective physical complaints are measured by the Giessen Subjective Complaints List (GBB-24) [48]. The four domains of complaints (fatigue, stomach problems, heart problems and joint pain) are rated on a five-point scale, ranging from 0 (“not existing”) to 4 (“strong”).

#### Utilization of psychosocial resources

Two adapted subscales of the Psychosocial Resource Utilization Questionnaire for Family Caregivers of People with Dementia (PRUQ) [42] are used to measure the utilization of resources of caregivers [additional file 1]. The adapted subscales “Utilization of resources related to well-being” and “Utilization of resources related to coping with daily hassles” consist of 9 and 15 items, respectively. Participants use a 5-point scale (1 = “never”, 5 = “very often”) to indicate the frequency with which they had utilized each resource (e.g. to do something for one’s own health and physical fitness) in the last 4 weeks for achieving a motivational goal (e.g. to feel good).

#### Caregiver self-efficacy and burden

Two subscales of the abbreviated German version of the Sense of Competence Questionnaire (SCQ-AV; subscales: “Satisfaction with one’s own performance as a caregiver” and “Consequences of involvement in care for the caregiver’s life”) [49] are used in this study. Items are rated on a 5-point scale (from “agree” to “disagree”).

#### Emotional well-being

A self-developed visual analogue scale (0 to 100, vertical) is used to assess emotional well-being [24, 27].

#### Coping with problems

The subscale “Negative Problem Orientation” of the Social Problem Solving Inventory – Revised Quik Score form (SPSI-R:S) [50] [51] is used to assess negative problem orientation. This subscale contains five items that are rated on a 5-point scale ranging from 0 (“not very true of me”) to 4 (“extremely true of me”). The total score ranges from 0 to 20.

#### Coping with burden of care

Based on the experience of our previous studies a single item (“How well are you able to cope with the care situation?”; from 0 (“very badly”) to 4 (“very well”) is used to measure coping with burden of care [24].

#### Positive aspects of caregiving

Psychosocial benefits of caregiving among family caregivers are assessed with six Items (Items 2, 3, 4, 7, 8, 9) of the Positive Aspects of Caregiving (PAC) scale [52]. Items are scored on a 5-point scale from 1 (“disagree a lot”) to 5 (“agree a lot”).

#### Perceived quality of care and abusive behaviour

A self-developed questionnaire with 22 items measures different indicators of quality of care (e.g. health care, nursing, environment, decubitus, forms of harmful behaviour and abuse by the caregiver). Items are rated on a 5 point-scale from 0 to 4 with different categories (e.g. “never” to very often / 3–7 times per week) (additional file 2).

#### Quality of relationship

The current and past quality of relationship is measured with two questions (“What is the quality of your current relationship with your relative?” and “What was the quality of your relationship with your relative before he/she needed care?”). Both questions are rated on a 5-point scale from 0 (“very bad”) to 4 (“very good”).

### Other measures

#### Caregiver characteristics

For caregivers, detailed conditions of the care situation, diseases, sleep quality, and health service use are assessed [23, 24].

#### Activities of daily living and cognitive functioning

For the care recipient characteristics, type of diseases, functional disability, health and care service use are assessed. Activities of daily living (ADL) are measured with the Barthel Index (BI) [53], higher cognitive functioning (comprehension, verbal expression, social interaction, problem solving, memory/learning/orientation, and vision/neglect) with the Extended Barthel Index (EBI) [54].

#### Cost effectiveness

The cost-effectiveness analysis is conducted from a health care perspective and a societal perspective with a time horizon of 3 to 12 months. The costs are recorded on the basis of statutory health insurance data and data provided by the caregivers. Additional information on non-reimbursed caregiver time and out-of-pocket expenditures are collected (e.g. types of daily assistance). Collection of cost data will follow established international standards using the costing methodology suggested by Drummond [13]. If participants agree, available data on medical resource utilization from the two cooperating statutory health insurances are included in the analyses. As a measure of effectiveness, subjective health-related quality of life is measured with the Veterans Rand 12-item Health Survey (VR-12) [55, 56]. Items of the VR-12 are summarized in two scores, a physical and mental component score. To perform the cost-effectiveness analysis, the incremental cost-effectiveness ratio (ICER) will be calculated, comparing the costs and outcomes of different modalities (interventions, routine care).

#### Satisfaction of patients and interventionists with the intervention

A set of questions is used to assess the satisfaction of caregivers with intervention 1 at t_1_, and with intervention 2 at t_2_. Six questions cover the general setup of the intervention (setting, number of sessions, and duration of a single session) and perceptions of helpful and unhelpful aspects of the intervention, further 24 items the competence and experience with the counsellor and therapist. In addition, three items of the Client Satisfaction Questionnaire (CSQ-8) [57] focus on the quality of service, and general satisfaction of the participant. After the follow-up (t_3_) the participants are asked to comment on the intervention on ten different aspects (ratings and open questions) from a retrospective perspective. In addition to the caregivers, all care counsellors in intervention 1 are asked for feedback (ratings and open questions) on their experience with the intervention approach (materials, feasibility, etc.), the training, supervision and supervisors after the initial training, the middle and end of the intervention period.

In intervention 2 Goal Attainment Scaling (GAS) [58] is used to evaluate participants’ personal goal attainment. During the first and/or second telephone sessions, the caregiver and the therapist identify the caregiver’s personal goals for the intervention 2. The steps of GAS are formulating goals, describing goals in observable terms, defining a hierarchy of goals and potential outcomes. In the last therapy session, therapists and caregivers rate the goal attainment.

### Process evaluation

Major goals of the process evaluation are to document how well the intervention was implemented as designed (domain 1 “Implementation”), to describe how caregivers participated in and responded to the intervention, including any variations across the two settings in intervention 1 (domain 2 “Participation and response”), and to describe and explore contextual factors that may influence the delivery or impact of the intervention (domain 3 “Context”) [59].

#### Intervention 1

Documentation of all contacts with caregivers by standardized documentation sheets (date, session duration, mode of contact, distance and travel time for home visits). To assess treatment fidelity, worksheets with information on key components of intervention 1 (selected goal(s), alternative solutions, the solution plan and goal attainment) are rated by independent raters. To control for effects related to counsellor characteristics, further counsellor data like the professional background (e.g. previous professional trainings, professional experience), motivation to participate in the study, the appraisal of the intervention, number of consultations within the study, counsellor self-efficacy, work-related sense of coherence, chronic stress, and compassion are evaluated.

#### Intervention 2

Implementation is assessed by standardized documentation sheets. Therapists record session date, session duration, if and why an appointment was changed, if and why a session was interrupted, and intervention and/or study drop-out. To assess treatment compliance, therapists use standardized documentation sheets to note session content, to rate main themes and intervention strategies of the session.

The Scale for the Multiperspective Assessment of General Change Mechanisms in Psychotherapy (SACiP) [45] is used to assess the mechanism of change from both therapists’ and patients’ perspectives. Therapists and caregivers rate the six scales (agreement on collaboration, resource activation, problem actuation, clarification of meaning, emotional bond and mastery) after each telephone session.

Patients’ expectations regarding therapy and outcome are measured by the “Patient Questionnaire on Therapy Expectation and Evaluation” (PATHEV) [60] before session 1 and after session 10. This questionnaire consists of 11 items and three subscales: hope of improvement, fear of change, and suitability. Treatment integrity, such as therapists’ adherence and competence, will also be judged by independent raters, who will be qualified to rate treatment adherence and competence by completing an intensive training, during which the therapy manual and the application of the rating scales will be explained. Audiotapes from the intervention 2 will be randomly selected for treatment integrity rating. The items developed for the adherence scale are based on the intervention modules described in the manual. Conceptualization of the competence scale is based on our previous studies [23, 61, 62].

### Participant timeline

After enrolment, all participants are assessed (-t_1_) and assigned (t_0_) to either the intervention or control arm of the study. During the first 3 months participants of the intervention group receive intervention 1 (care counselling). During the next 6 months caregivers in the intervention group receive CBT (intervention 2) over 6 months or, alternatively, a follow-up call delivered by the counsellor of intervention 1. All outcomes are assessed again after 3 months (t_1_), 9 months (t_2_), and 15 months (t_3_) (Fig. 2).

**Fig. 2 Fig2:**
[figure not shown]
Study design and planned number of participants at each stage. Note. State 1 = Bavaria, state 2 = Baden- Württemberg

If caregiving ends during the intervention period (e.g. because of death of care recipient, transition to nursing home) we offer a (continuation) of the CBT intervention based on a case-by-case decision. All participants who end caregiving before t_3_ are followed up with a modified questionnaire. These post-caregiving data will be not included in the main outcome analysis.

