**Methods/ design:**

A pragmatic randomised controlled trial with 572 caregivers of older adults (≥ 60 years) receiving benefits of one of the two participating long-term care insurances. Participants are assigned (t_0_) to either the ReDiCare intervention or a control group receiving routine care and counselling. Data are collected at baseline (-t_1_), 3-month (t_1_), 9-month (t_2_) and 15-month (t_3_). The 9-month post-intervention assessment (t_2_) is the primary endpoint to evaluate the results on the primary and secondary outcomes, measured by self-reported questionnaires. Depressive symptoms measured with the CES-D are the primary outcome. The main secondary outcomes are physical complaints, utilization of psychosocial resources, caregiver self-efficacy and burden, positive aspects of caregiving and perceived care quality. A process evaluation, including audio tapes, self-report questionnaires and documentation will be conducted to examine internal and external validity of the intervention. Data on direct and indirect costs are collected for the (health) economic evaluation, using a health care perspective and a societal perspective.

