**Intervention 2: Cognitive behavioural therapy** (delivered in 12 telephone contacts by psychotherapists) 1. ***Basic elements:*** creating therapeutic alliance, individual goal setting, problem analyses, resource activation, handling conflicts and crises. 2. ***Psychoeducation:*** information provision on disease related aspects (e.g. dementia) and caregiving to improve coping with caregiving (e.g. better acceptance of care recipient’s chronic condition). 3. ***Changing dysfunctional cognitions:*** developing alternative and helpful cognitions (e.g. through Socratic dialogue, guided discovery) and their implementation in daily life. 4. ***Dealing with challenging behaviour of the care recipient:*** strengthening problem-solving abilities through problem and behaviour analysis and problem-solving training. 5. ***Stress-management and emotion regulation:*** facilitating acceptance of negative emotions (e.g. anger) as normal and adaptive self-reflection from a self-distanced perspective, developing emotion-regulation strategies, working on general levels of tension and stress. 6. ***Self-care and value-based activities:*** understanding the importance of positive activities in managing mood (e.g. with a weekly diary), developing, planning, and implementing health-promoting activities in everyday life, coping with feelings like guilt as barriers for self-care (e.g. through acceptance). 7. ***Coping with change, grief, and loss:*** discussing experiences of loss and facilitating emotion-based strategies and acceptance to cope with changes caused by the care recipient’s chronic condition (e.g. changes in the relationship with the care recipient, social isolation because friends have pulled back or lack of time to spend with relatives or friends) 8. ***Informal and professional support:*** discussing possibilities of assistance and help by friends, relatives, and volunteers as well as professional services, overcoming possible barriers for accepting help (e.g. feelings of guilt) with CBT strategies like cognitive restructuring. 9. ***Limits of caregiving:*** identifying boundaries and personal limits to what can be provided at home (e.g. when caregiver stress leads to abusive behaviour, violence by the care recipient), preparing the transition from home care to formal care (e.g. nursing home). 10. ***Evaluation:*** summarizing achieved changes and goals, discussing plans and possible next steps.

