### Sample size

Sample size calculation is based on analyses of covariance (ANCOVA) to compare post-interventions scores of both groups at t_2_ using -t_1_ scores as independent variables. The sample size for the ANCOVA was calculated in a two-step method as proposed by Borm et al. [63]: (1) Calculation of the sample size n as if a t-test on the follow-up scores was carried out, (2) the number of subjects was then multiplied by a “design factor” [(1 – ρ^2^)*n; ρ = correlation between baseline and follow-up scores] to produce the number of subjects required for the ANCOVA.

The calculation is based on data of previous studies [18, 19, 24] with informal caregivers and the following assumptions: (a) An aimed relevant improvement of the CES-D scores of 3 points compared to the control condition (corresponding effect size Cohen’s d of 0.34); (b) depressive symptoms at t_2_ (control: M = 21.0, SD = 10.1; intervention: M = 18.0, SD = 7.6); (c) a correlation ρ = 0.49 between baseline and follow-up measures (the lowest ρ was used); (d) 1- β = .80 (power); and (e) α = .05 for a two-sided t test, (f) a ratio of n (control) / n (intervention) = 1.00. (1) Using a formula for a two-sample t-test (G*Power Vs. 3.1.9.2) [64] the required total sample size is 282. (2) The required adjusted sample size for ANCOVA with the same power as the t-test is 216 [design factor: (1- 0.49^2^)*n (total)].

Possible different strategies to promote study participation of the two participating insurances are an element of uncertainty in the sample size calculation. Therefore, we added an additional 10% to the calculated 216 participants to compensate a possible shift in variance. Taking this into account, the aimed sample size is 238.

Based on the same assumptions (two-sided t-test, α = .05, 1- β = .80, d = .34) and data of our previous work, the correlations between baseline and follow-up measures of secondary outcomes are expected to be ρ = .40 (VAS Mood), ρ = 0.72 (GBB-24), 0.59 (SPSI-R:S / Subscale “Negative problem orientation”), and ρ = 0.70 (SCQ-AB / Subscale “satisfaction with one’s own performance”). Because of these higher correlations in comparison to the CES-D we assumed that the total sample size of 216 participants will be sufficient to detect at least moderate effects in all secondary outcome measures except the ‘VAS Mood’. For this scale, the aimed sample size of 238 is still sufficient. 

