### Statistical methods

Comparability in all baseline parameters of the two randomized study groups will be described. For the intention-to-treat (ITT) analysis, missing values for withdrawn subjects or participants with missing data at t_1_ to t_3_ will be imputed by MLMI (Maximum Likelihood Multiple Imputation). For each outcome, ten data sets with imputed values (based on linear regression prediction) will be generated and the results pooled to obtain final estimates.

Inference statistic will be performed according to the variable type with χ^2^-test or Fisher exact tests for categorical variables, Mann–Whitney U tests for ordinal or not normally distributed continuous variables, and t-tests for normally distributed continuous variables. Group differences of the confirmatory endpoints will be tested with ANCOVAs (Analyses of Covariance) considering relevant baseline covariates on a two-sided significance level of 5% taking multiple testing into account. Effects of the intervention on secondary outcomes will be analysed accordingly. Additionally, random coefficient models and latent change analyses will be applied to estimate group effects in longitudinal data structures with repeated measurements. The health economic evaluation will include analyses of intervention costs, cost-effectiveness, and possible cost-benefits.

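### The rule that sets aside data collected after caregiving ends is not reconciled with the declared intention-to-treat analysis, and neither way of applying it gives the ITT effect at t2

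*Protocol article*

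**What the plan says.** Four parts of the protocol article bear on this.

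- **Participant timeline (text after Fig. 2).** The named routes out of caregiving are in the clause "If caregiving ends during the intervention period (e.g. because of death of care recipient, transition to nursing home"; CBT may be offered or continued afterwards, case by case. Then: "All participants who end caregiving before t_3_ are followed up with a modified questionnaire", and directly after that, "These post-caregiving data will be not included in the main outcome analysis".
- **Statistical methods.** "For the intention-to-treat (ITT) analysis, missing values for withdrawn subjects or participants with missing data at t_1_ to t_3_ will be imputed by MLMI". Caregivers who stop caregiving but stay in follow-up are not mentioned.
- **Abstract, Methods/design.** "The 9-month post-intervention assessment (t_2_) is the primary endpoint", with the CES-D as primary outcome. Every stop before t2 therefore touches the primary comparison.
- **Table 1, Intervention 2.** The ninth CBT module, on limits of caregiving, includes "preparing the transition from home care to formal care (e.g. nursing home".

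The Objectives section states the aim as the effect of the stepped intervention on depressive symptoms against control. It does not restrict that aim to people who are still caregiving.

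**The concern.** Whether caregiving has ended by t2 is known only after randomisation. A rule that sets outcomes aside on that basis changes what the primary comparison estimates, and randomisation no longer protects the comparison if the arms differ in who stops or in how many stop. Only the intervention arm can receive a CBT module that deals with the move to formal care, so a difference in nursing-home transitions is plausible. Death of the care recipient is less plausibly affected.

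The primary outcome gives no reason for the restriction. The CES-D rates depressive symptoms and has the same meaning as a scale whether or not the respondent is caregiving. That is not true of the caregiving-specific scales, such as the SCQ subscales, PAC and perceived quality of care. At stake is whether the confirmatory result can be read as the ITT effect that the protocol declares.

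**Working it through.** **1. The two rules side by side.** A caregiver who has stopped, remains in follow-up and returns the modified questionnaire has neither withdrawn nor, if the questionnaire carries the CES-D, a missing value. The timeline rule sets that value aside; the imputation rule does not say what happens next. Two readings are possible.

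- *Dropped.* The comparison is among continuers only, a group defined after randomisation.
- *Set to missing and imputed.* Everyone stays in, but observed values are replaced by predictions. The target becomes the effect had caregiving continued, under missing-at-random. The protocol states no such target.

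Under both readings the result differs from the ITT effect.

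**2. Do the eligibility criteria close the gap?** They exclude a probable nursing-home move within 3 months, palliative care, and terminal illness with life expectancy under 6 months. The primary endpoint is at 9 months, so exits between those windows and t2 remain possible.

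**3. The plan's own figures.** The target is "An aimed relevant improvement of the CES-D scores of 3 points compared to the control condition (corresponding effect size Cohen’s d of 0.34"). From the Sample size section, the t2 SDs are 10.1 and 7.6 and ρ = 0.49.

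- Pooled SD = √((10.1² + 7.6²)/2) = 8.94, so d = 3/8.94 = 0.336.
- Exact two-sample t-test, two-sided 0.05, power 0.80: total N = 282, as stated.
- ANCOVA factor: 282 × (1 − 0.49²) = 214.3, against the stated 216.
- 216 × 1.10 = 237.6, so 238, as stated.
- SE of the adjusted contrast at N = 238: 8.94 × √(1 − 0.49²) × √(2/119) = 1.01.

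**4. Illustration, dropping reading only.** Let p be the share in an arm who have stopped by t2, and δ the mean CES-D of stoppers minus continuers, taken as equal in both arms. The continuers' mean is the full-arm mean minus pδ. The continuers-only contrast (intervention minus control) therefore differs from the ITT contrast by −δ × (p_int − p_ctl). The document gives neither δ nor p, so the values below are assumptions.

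| δ | p_int − p_ctl | Absolute shift | Share of 3 points | Two-sided type I error at N = 238 |
|---|---|---|---|---|
| 5 | 5 pp | 0.25 | 8% | 5.7% |
| 8 | 10 pp | 0.80 | 27% | 12.4% |

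The last column assumes no true effect and uses the SE of 1.01.

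Equal exit rates do not guarantee safety. With the same p in both arms, the absolute shift is p times the between-arm difference in δ: 0.10 × 3 = 0.3 up to 0.20 × 6 = 1.2 points, again on assumed values.

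**5. Imputation reading.** The formula in step 4 does not carry over. The departure from the ITT effect depends on the imputation model and on how far stoppers' real scores lie from their predicted ones. The document gives nothing from which to size it.

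**The case against.** The strongest defence is that the timeline rule excludes data and not people. Read with the ITT statement, it may mean that every randomised caregiver stays in and post-caregiving values are imputed. That is a pre-specified, openly stated choice in a trial of support for people who are caregiving, and bereavement or placement does change what a depression score reflects. This stands as far as it goes. A reader might infer that participants are removed and that ITT fails for that reason, but the text does not establish removal. What remains is that the protocol neither chooses between the readings nor states the hypothetical target that the gentler one implies.

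Other tempting inferences also go too far.

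- *The intervention acts on stopping in several ways.* Only the module on limits of caregiving bears on it, through nursing-home transition. The module on grief and loss concerns changes caused by the care recipient's condition; it is not described as affecting whether caregiving ends. CBT is itself an optional second step with modules combined by need, which limits how far the arms could diverge.
- *The CES-D after caregiving ends is already in hand.* The contents of the modified questionnaire are not given.
- *Power is lost against plan.* The 238 is a completer target, already net of assumed dropout. Whether that dropout includes ended caregiving is not stated, and Fig. 2 is not available.
- *There is no sensitivity analysis.* One may sit in the full protocol or analysis plan, so its absence here is not held against the trial.

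The eligibility exclusions should limit early exits, but they stop short of 9 months.

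**Conclusion.** The point holds in this form: the timeline rule and the ITT declaration are unreconciled, and the t2 CES-D comparison is not the declared ITT effect under either reading. That conclusion rests on the text alone.

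The size does not. The document gives no rate at which caregiving ends, no split by arm and no outcome data for those who stop. The shift of 0.25 to 0.8 points applies only if stoppers are dropped, and only under the assumed exit-rate and CES-D differences. The direction is also open: stoppers may score higher, for example after bereavement, or lower, for example through relief after placement, and either arm may have more of them.

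**What to change.** Reconcile the Participant timeline and Statistical methods sections before the data are unblinded.

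1. State that the primary ITT analysis uses every randomised caregiver's observed t2 CES-D, whether or not caregiving has ended. Those with no t2 CES-D fall under the existing imputation rule.
2. Confirm that the modified questionnaire contains the CES-D.
3. Report by arm the number who stopped caregiving before t2, and the reason (death of the care recipient, nursing-home transition, other).
4. Keep the analysis of those still caregiving at t2 as supportive, and say whether stoppers are excluded or imputed in it.
5. Retain the restriction for the caregiving-specific scales.

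**Cost.** If the CES-D is in the modified questionnaire, this is a short change of text: follow-up of stoppers is already planned and no stated sample size changes. If it is not, the scale has to be added, and the scores of stoppers already assessed without it stay missing. The real downside is interpretive. The primary estimate will also reflect mood after bereavement or placement, which is why the supportive analysis should be reported beside it.
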